## Monitoring

### Data monitoring

To assure the quality of the data collected, the protocol study team will provide training specific to accuracy of data acquisition for the site study team at each study site. The protocol study team will design CRFs, which a subset of study sites will subsequently pilot to minimize the potential for errors. Additionally, the protocol study team will allocate sufficient funds to allow for quality data collection. The site study team will re-abstract a subsample of their own charts and assess the error rate. Re-abstraction will focus on critical data elements related to the primary and secondary objectives of the protocol. The protocol study team will base the number of charts a study site re-abstracts, for each study period, on the number of patients enrolled at the mid-point in the study period as shown below:

**Table Taba:** 

No. of patients enrolled during the study period	No. of charts to be re-abstracted
0	0
1–14	1
15–24	2
25–34	3
35–44	4
45–54	5

The DCC will provide study sites with the randomly selected subject IDs for re-abstraction. The site study team will identify an independent site quality control (QC) abstractor who will re-abstract and enter data into the electronic data capture system (EDC) only for the QC process and will not abstract study data while QC activities are taking place. The DCC will generate a discrepancy report comparing study data abstracted by the study site with the source information abstracted by the independent site QC abstractor. The DCC will hold a QC Review Meeting with the site study team, to include the independent site QC abstractor, research coordinator, and original site abstractor(s) to review the discrepancies and identify errors. Together they will discuss and document the corrective action for each error identified. The DCC will create manual queries in the EDC to make any necessary corrections to the data that QC review members identify. The protocol study team will provide study sites that have an error rate above the predefined threshold with additional training, a site-specific assessment of the data collection process, and suggestions for process improvement. The protocol study team will track study sites by their error rates. The protocol study team will share practices of those study sites with exceptionally low error rates with study sites working to improve their own process. The protocol study team will review error rates and re-abstraction data during monthly team calls. If errors exceed the predefined threshold on 2 consecutive reviews, a remediation plan will be requested and shared with the study sponsor. Study sites that have an error rate above the predefined threshold will receive additional training, a site-specific assessment of the data collection process, and suggestions for process improvement.

#### Interim analyses

One interim analysis of efficacy of the primary endpoint (as well as associated safety data) will be performed when the assessment of the primary endpoint is completed in approximately 50% of enrolled infants with NOWS. The DSMB will review the results of the interim analysis. Based on pre-specified study stopping rules outlined in the SAP, the DSMB will provide a recommendation to the protocol study team and study sponsor regarding stopping the study early due to evidence of efficacy or continuing enrollment as planned.

### Adverse events

#### Definition of adverse events and serious adverse events

AE: AE means any untoward medical occurrence associated with the use of an intervention in humans, whether or not considered study intervention related.

AEs of special interest (AESI): AESIs will include seizures, excessive weight loss (more than 15% from birthweight), and respiratory insufficiency that occur during the initial hospitalization, after study enrollment, through hospital discharge.

Serious adverse event (SAE): An AE is considered “serious” if, in the view of either the site PI or the study sponsor, it results in any of the following outcomes:DeathLife-threatening AE (life-threatening means that the study participant was, in the opinion of the site PI or study sponsor, at immediate risk of death from the reaction as it occurred and required intervention)Persistent or significant incapacity or substantial disruption of the ability to conduct normal life functionsInpatient hospitalization or prolongation of existing hospitalizationImportant medical event that may not result in one of the above outcomes but may jeopardize the health of the study participant or require medical or surgical intervention to prevent 1 of the outcomes listed in the above definition of serious event

#### Classification of an adverse event

##### Severity of event

For AEs, the site PI will use the following guidelines to describe severity.Mild: Events require minimal or no treatment and do not interfere with the participant’s daily activities.Moderate: Events result in a low level of inconvenience or concern with the therapeutic measures. Moderate events may cause some interference with functioning.Severe: Events interrupt a participant’s usual daily activity and may require systemic drug therapy or other treatment. Severe events are usually potentially life-threatening or incapacitating. Of note, the term “severe” does not necessarily equate to “serious.”

##### Relationship to study intervention

The site study team will grade the degree of certainty about causality by using the below categories:Definitely related—There is a definite temporal and logical/medical relationship to a study procedure.Probably related—There is a strong temporal relationship to study procedure and another cause of event is unlikely or significantly less likely.Possibly related—There is a strong temporal relationship to the study procedure and another cause of event is equally or less likely compared to the potential relationship to study procedure.Unlikely related—There is little or no temporal relationship to the study procedure and/or a more likely other cause of event exists.Not related—There is not a reasonable possibility that the study procedures caused the AE, there is no temporal relationship between the study procedures and AE onset, or an alternate etiology has been established.

#### Collection of adverse event assessment and follow-up

For this study, the site study team will collect adverse event data on all enrolled infants:From enrollment to hospital discharge:◦ Seizure (AESI)◦ Respiratory insufficiency (AESI)◦ Weight loss > 15% of birthweight (AESI)◦ Death (SAE)◦ Life-threatening AE (life-threatening means that the study participant was, in the opinion of the site PI or study sponsor, at immediate risk of death from the reaction as it occurred and required intervention) (SAE)◦ Persistent or significant incapacity or substantial disruption of the ability to conduct normal life functions (SAE)◦ Inpatient hospitalization or prolongation of existing hospitalization (SAE)◦ Important medical event that may not result in one of the above outcomes but may jeopardize the health of the study participant or require medical or surgical intervention to prevent 1 of the outcomes listed in the above definition of serious event (SAE)From discharge through 3 months of age:◦ Death (SAE)◦ Life-threatening AE (life-threatening means that the study participant was, in the opinion of the site PI or study sponsor, at immediate risk of death from the reaction as it occurred and required intervention) (SAE)◦ Persistent or significant incapacity or substantial disruption of the ability to conduct normal life functions (SAE)◦ Inpatient hospitalization or prolongation of existing hospitalization (SAE)◦ Important medical event that may not result in one of the above outcomes but may jeopardize the health of the study participant or require medical or surgical intervention to prevent 1 of the outcomes listed in the above definition of serious event (SAE)

The occurrence of an AESI or SAE may come to the attention of site study team during the hospital stay, by the clinical team, or upon reviewing data. The site study team will capture all AESIs or SAEs on the appropriate CRF. Information to be collected includes event description, date/time of onset, date/time of resolution, clinician’s assessment of severity, relationship to study intervention, and time of resolution/stabilization of the AE. The site study team must follow all AESIs until the AESI meets one of the following criteria: resolution, the condition stabilizes, the AESI is otherwise explained or is judged by the protocol study team to be no longer clinically significant, or the participant is lost to follow-up.

Each of the site PIs (or designee) is responsible for ensuring that the completed AE form along with additional laboratory findings or other documentation required to describe the event is submitted to the DCC as specified in the manual of procedures. The study participant records are identified by study ID number and all other identifying information is stripped from the forms.

#### Reporting of adverse events

Cumulative AE data are reviewed by the DSMB at scheduled meetings during the study. The DCC will prepare reports of the study for review by the DSMB. Any AEs may be reported to the DSMB at other times at the request of NICHD.

The DCC will report safety events to the sIRB as needed.

### Protocol deviations

The DCC will monitor protocol deviations per study site in relation to the number of participants enrolled. All study sites will receive re-education via regularly scheduled teleconferences to help other study sites prevent similar deviations. If a particular deviation is recurrent at one study site or across the study sites, the DCC may implement operational tools, such as additional reminders, source document worksheets, and/or checklists, to reduce the likelihood of deviations. The DCC will review protocol deviations throughout the study, and it may schedule additional on-site visits, as needed, to review regulatory documents, data points, key issues, etc. or to retrain site study team to improve processes and provide additional education.

#### Protocol deviations definitions

Protocol deviation—The site PI and site study team will conduct the study in accordance with the protocol; no deviations from the protocol are permitted. Any change, divergence, or departure from the study design or procedures constitutes a protocol deviation. As a result of any deviation, corrective actions will be developed by the study site and implemented promptly.

Major protocol deviation (protocol violation)—A protocol violation is a deviation from the sIRB approved protocol that may affect the subject’s rights, safety, or well-being and/or the completeness, accuracy, and reliability of the study data. In addition, protocol violations include willful or knowing breaches of human subject protection regulations, or policies, any action that is inconsistent with the NIH Human Research Protection Program’s research, medical, and ethical principles, and a serious or continuing noncompliance with federal, state, local, or institutional human subject protection regulations, policies, or procedures.

#### Reporting and management of protocol deviations

The site PI has the responsibility to identify, document, and report protocol deviations as directed by the study sponsor. However, protocol deviations may also be identified during site monitoring visits or during other forms of study conduct review.

## Ethics and dissemination

### Research ethics approval and IND exempt status

A sIRB will be used for all study sites.

#### Waiver of IND

The study will be exempt from IND based upon the following criteria, all of which are true in this investigation [21].The drug product is lawfully marketed in the USA.The investigation is not intended to be reported to the US Food and Drug Administration as a well-controlled study in support of a new indication and there is no intent to use it to support any other significant change in the labeling of the drug.The investigation is not intended to support a significant change in the advertising for the drug.The investigation does not involve a route of administration, dose, patient population, or other factor that significantly increases the risk (or decreases the acceptability of the risk) associated with the use of the drug product (21 CFR 312.2(b)(1)(iii)).The investigation is conducted in compliance with the requirements for review by an IRB (21 CFR part 56) and with the requirements for informed consent (21 CFR part 50).The investigation is conducted in compliance with the requirements of § 312.7 (i.e., the investigation is not intended to promote or commercialize the drug product).

The clinical trial employs a pragmatic approach in which study sites will largely use their preferred opioid (morphine, methadone, buprenorphine) in usual care excipients and at doses which they use in the clinical care context. The change of dosing approach is not expected to have a different risk profile based upon treatment allocation.

### Consent or assent

#### Waiver of consent for in-hospital participation

The use of a cluster crossover design for this study will allow for randomization of the study intervention at the level of the study site. Study sites will adhere to their assigned approach for the pharmacologic treatment of all infants with NOWS cared for at their site throughout the study. Maintaining a generalizable study population will be essential to ensure that the results of this study will inform clinical care. Variation in antenatal exposure, from consistent daily exposure to medical treatment of opioid use disorder to active use of illicit opioids, complicates neonatal opioid withdrawal and may impact an infant’s response to the approach to pharmacologic treatment. As such, we request a waiver of consent from the sIRB for this study to minimize the risk of biasing the sample towards stable maternal/infant dyads with less severe opioid dependency and comorbidities.

A cluster-randomized clinical trial may proceed without individual consent if Common Rule conditions for a waiver of consent are satisfied, and participants (or legally authorized representatives) are provided with a description of the study intervention to which their cluster has been randomized. As stated in Code of Federal Regulations [45 CFR 46.116 (d)], an sIRB may approve a consent procedure that does not include, or that alters, some or all of the elements of informed consent set forth in this section, or waive the requirements to obtain informed consent, provided the sIRB finds and documents that all of the following conditions are met:The research involves no more than minimal risk to the participants.The waiver or alteration will not adversely affect the rights and welfare of the participants.The research could not practicably be carried out without the waiver or alteration.Whenever appropriate, the study team will provide participants with additional pertinent information after participation.

The justification for a waiver of informed consent from caregiver(s) for the previously outlined study objectives meets the above criteria as follows:The research involves no more than minimal risk to the participants.Both approaches to pharmacologic treatment (i.e., the symptom-based dosing approach and scheduled opioid taper approach) are currently used at sites across the country, and the optimal approach to pharmacologic treatment for infants with NOWS is unknown. The protocol study team has utilized recommendations from the AAP to define the primary outcome to further facilitate safe discharge practices for all infants with NOWS. Undertreatment and overtreatment will be minimized by the study parameters developed by the protocol study team and a DSMB will be engaged to identify any risk concerns throughout the study. The usual approach to management of NOWS is protocol-driven based upon a site level therapeutic approach. Dosing approach (symptom versus scheduled) is not decided at the level of the individual patient nor at the discretion of an individual practitioner. Thus, the role of removing individual physician discretion for specific infants, a commonly cited criteria against waiver of consent, is not an issue in NOWS in which dosing approach is determined at the facility level. This clinical trial will employ two widely accepted dosing approaches. In addition, the treatment of NOWS in the inpatient setting is extremely safe regardless of the opioid employed or dosing regimen. This is due to drug dosing that is directly tied to symptom scores every 4 h, signs of excess sedation being evident much before respiratory depression, and careful respiratory monitoring in an inpatient setting.The waiver or alteration will not adversely affect the rights and welfare of the participants.As the best pharmacologic management for infants with NOWS is unknown, there is no universally accepted standard approach, and both management strategies are currently being used at sites across the country. Therefore, participants receiving care via either approach to pharmacologic treatment should not have their rights and welfare adversely affected.The site research team could not practicably carry out this trial without the waiver or alteration.Recent clinical trials in NOWS for which individual patient consent to an altered therapeutic regimen (NCT04214834, 04104646) have encountered a patient consent rate of only 20–30% of those eligible. Though the patient parental characteristics of those who have declined participation cannot be collected in systematic fashion, clinical trialists at these sites have noted those declining tend to have more polysubstance abuse, have higher use of prescribed benzodiazepines and psychotropics, are less likely to be in an outpatient opioid use disorder program, and often have impulse control as part of a comorbid psychiatric diagnosis. Most of these factors have been linked to worse outcomes (as measured by symptom scores and length of treatment for infants). Large (for NOWS) randomized trials with individual level consent have all tended to have enrolled mothers with less of the risk factors listed above [22–24]. The feasibility and generalizability of this trial would be limited if obtaining informed consent were required. It is highly possible that infants with antenatal exposure to illicit or misused opioids may respond differently to symptom-based dosing approach than infants with antenatal exposure to medications for opioid use disorder (MOUD). The goal of this research is to identify a generalizable approach to pharmacologic treatment for infants with NOWS. Enrolling only a consented population will likely bias the study results towards infants born to women who are stable on MOUD and miss a high-risk sub-population of infants with NOWS. This could be particularly problematic in this trial where there may be variation in the response to treatment. Each study site will use the assigned approach to care for all infants with NOWS throughout the trial. Therefore, obtaining consent would not alter the care approach used for the infant. Thus, the benefits afforded by using a waiver of consent outweigh the risks to the infant receiving the same treatment.Whenever appropriate the study team will provide participants with additional pertinent information after participation.Throughout the study, the site study team will provide participants with additional pertinent information when appropriate. The site study team will (a) give to the caregiver(s) of all infants with NOWS who are cared for at the study site throughout the study and/or (b) post (as an enlarged copy) in appropriate location(s) readily visible to caregivers. This will fulfill the suggested framework [25] of participants being “provided with a detailed description of the study interventions to which their cluster has been randomized.”

Additional consent provisions for collection and use of participant data for neurodevelopmental follow-up and biological specimens may be added.

### Records retention

For NIH, grantees must retain records for a period of 3 years from the date of Federal Financial Report (FFR) submission.

## Statistical considerations and analytical plans

### Overview

This section briefly describes the analysis plan that will be followed for this study. A statistical analysis plan (SAP) will also be developed and finalized prior to database lock. The SAP will include a detailed description of each analysis and will precede any analyses described in this section.

### Analysis populations

The following analysis populations will include all randomized study sites that enrolled participants, regardless of the degree of adherence to the study interventions.

Intention-to-treat population (ITT): All enrolled participants at a study site during the study. Each participant will be analyzed according to the study intervention that the study site was assigned at the time the participant was born.

Intention-to-treat population—pharmacologically treated (ITT-PT): All participants in the ITT population who were pharmacologically treated at a study site during the study. Each participant will be analyzed according to the study intervention that the study site was assigned at the time the participant was born.

Intention-to-treat population—pharmacologically treated with symptom-based dosing approach (ITT-PT1): All participants included in the ITT-PT population who were pharmacologically treated using a symptom-based dosing approach.

Intention-to-treat population—pharmacologically treated with scheduled opioid taper approach (ITT-PT2): All participants included in the ITT-PT population who were pharmacologically treated using a scheduled opioid taper approach.

Secondary objective #8	ITT-PT2	Cessation of opioid treatment due to excessive sedation (yes/no)
Secondary objective #9	ITT-PT	Inpatient composite safety outcome (present/absent), defined as the occurrence of the following between birth and hospital discharge: • Seizures • Excessive weight loss more than 15% from birthweight Inpatient composite critical safety outcome (present/absent), defined as the occurrence of the following between birth and hospital discharge: • Non-accidental trauma • Death Outpatient composite safety outcome (present/absent), defined as the occurrence of the following between hospital discharge and 3 months of age: • Acute/urgent care or emergency room visits • Hospital readmissions Outpatient composite critical safety outcome (present/absent), defined as the occurrence of the following between hospital discharge and 3 months of age: • Non-accidental trauma • Death

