### Secondary hypothesis

All enrolled infants:To compare the length of time from birth until medically ready for discharge between infants with NOWS who are assessed and managed with FNAST and managed for NOWS with either a symptom-based dosing approach or a scheduled opioid taper approachTo compare the receipt of pharmacologic treatment for NOWS between infants managed for NOWS with either a symptom-based dosing approach or a scheduled opioid taper approachTo compare the length of hospital stay between infants managed for NOWS with either a symptom-based dosing approach or a scheduled opioid taper approachTo compare safety outcomes during the first 3 months of life between infants with NOWS who were managed with either a symptom-based dosing approach or a scheduled opioid taper approach

All enrolled infants who were pharmacologically treated:5.To compare the total number of opioid doses administered between infants with NOWS who were pharmacologically treated with either a symptom-based dosing approach or a scheduled opioid taper approach6.To compare the receipt of secondary medications between infants with NOWS who were pharmacologically treated with either a symptom-based dosing approach or a scheduled opioid taper approach7.To evaluate the proportion of infants with NOWS who were initially pharmacologically treated with a symptom-based dosing approach but transitioned to a scheduled opioid taper due to persistent signs of withdrawal8.To evaluate the proportion of infants with NOWS who were initially pharmacologically treated with a scheduled opioid taper but stopped treatment due to excessive sedation or respiratory depression9.To compare safety outcomes during the first 3 months of life between infants with NOWS who were pharmacologically treated with either a symptom-based dosing approach or a scheduled opioid taper approach

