### Secondary endpoints

All enrolled infants:Receipt of pharmacologic treatment (yes/no)Time from birth until hospital discharge (days)Inpatient composite safety outcome (present/absent)◦ Seizures◦ Excessive weight loss more than 15% from birthweightInpatient composite critical safety outcome (present/absent)◦ Non-accidental trauma◦ DeathOutpatient composite safety outcome (present/absent)◦ Acute/urgent care or emergency room visits◦ Hospital readmissionsOutpatient composite critical safety outcome (present/absent)◦ Non-accidental trauma◦ Death

Among all enrolled infants who were pharmacologically treated:Number of doses of primary medication administered (count)Receipt of secondary medications (yes/no)Inpatient composite safety outcome (present/absent)◦ Seizures◦ Excessive weight loss more than 15% from birthweightInpatient composite critical safety outcome (present/absent)◦ Non-accidental trauma◦ DeathOutpatient composite safety outcome (present/absent)◦ Acute/urgent care or emergency room visits◦ Hospital readmissionsOutpatient composite critical safety outcome (present/absent)◦ Non-accidental trauma◦ Death

Among all enrolled infants who were initially pharmacologically treated with a symptom-based dosing approach:Transition to an opioid taper due to persistent signs of withdrawal (yes/no)

Among all enrolled infants who were initially pharmacologically treated with a scheduled opioid taper approach:Cessation of opioid treatment due to excessive sedation or respiratory depression (yes/no)

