Secondary objective #5	Number of doses of primary medication administered	ITT-PT (stratified by type of medication)	GLMM • Distribution: negative binomial • Link function: log	Adjusted RR of doses of primary medication administered between infants who were pharmacologically treated with a symptom-based dosing approach to infants who were pharmacologically treated with a scheduled opioid taper approach
Secondary objective #6	Receipt of secondary medications	ITT-PT	GLMM • Distribution: binary • Link function: log	Adjusted relative risk of receipt of secondary medication between infants who were pharmacologically treated with a symptom-based dosing approach to infants who were pharmacologically treated with a scheduled opioid taper approach
Secondary objective #7	Transitioned to an opioid taper due to persistent signs of withdrawal	ITT-PT1	Descriptive statistics	Percentage of infants who were initially pharmacologically treated with a symptom-based dosing approach but transitioned to an opioid taper due to persistent signs of withdrawal
Secondary objective #8	Cessation of opioid treatment due to excessive sedation	ITT-PT2	Descriptive statistics	Percentage of infants who were initially pharmacologically treated with a scheduled opioid taper approach but stopped treatment due to excessive sedation
Secondary objective #9	• Inpatient composite safety outcome • Inpatient critical safety outcome • Outpatient composite safety outcome • Outpatient critical safety outcome	ITT-PT	Descriptive statistics	Percentage of infants who were pharmacologically treated and who met each endpoint will be summarized by study intervention

Similar to the sub-group analyses performed for the primary objective outlined in the Primary analysis of primary objective section, sub-group analyses will also be conducted for each secondary endpoint to determine if the intervention effect within each assessment and management approach is modified by the study period in which the participant was born.

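### Secondary objective #8 includes stops for respiratory depression in the objective and endpoint list, but Tables 3 and 4 count excessive sedation only

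*Protocol article*

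**What the plan says.** The protocol article describes secondary objective #8 in four places.

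- Secondary hypothesis, item 8: infants "initially pharmacologically treated with a scheduled opioid taper but stopped treatment due to excessive sedation or respiratory depression".
- Secondary endpoints: "Cessation of opioid treatment due to excessive sedation or respiratory depression (yes/no".
- Endpoints, Table 3: "Cessation of opioid treatment due to excessive sedation (yes/no", in the ITT-PT2 population.
- Analyses of secondary objectives, Table 4: the estimate is the percentage of infants "initially pharmacologically treated with a scheduled opioid taper approach but stopped treatment due to excessive sedation", by descriptive statistics.

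Analysis populations defines ITT-PT2 as "All participants included in the ITT-PT population who were pharmacologically treated using a scheduled opioid taper approach".

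Respiratory events also appear in the adverse event sections. Among the events of special interest, "AESIs will include seizures, excessive weight loss (more than 15% from birthweight), and respiratory insufficiency" are named. They are collected on all enrolled infants from enrollment to discharge. The inpatient safety composite in Table 3 uses seizures and weight loss but not respiratory insufficiency.

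**The concern.** Two of the four statements include respiratory depression as a reason for stopping and two do not, so an analyst cannot follow all four. Tables 3 and 4 are where the article fixes endpoint, population and estimate, so the narrower wording is the one likely to be programmed. A stop recorded as due to respiratory depression would then meet the stated objective and be missing from its result.

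This matters because the trial hypothesizes that symptom-based dosing shortens time to medical readiness safely, and #8 is the one listed endpoint on over-treatment with opioid. If it is reported under the objective's title but counted by the table's rule, the published percentage would be too low whenever such a stop occurs, and a reader could not tell.

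**Working it through.** **Step 1. Set the four statements side by side.**

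| Place | Excessive sedation | Respiratory depression | Infants covered |
|---|---|---|---|
| Secondary hypothesis, item 8 | yes | yes | initially on taper |
| Secondary endpoints | yes | yes | initially on taper |
| Table 3 | yes | no | ITT-PT2 |
| Table 4 | yes | no | initially on taper, ITT-PT2 |

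The reasons counted differ. The restriction to taper infants is common to all four, so the tables did not introduce it.

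**Step 2. Could the tables be shorthand?** Table 3 generally says more than the endpoint list. It adds how withdrawn participants are handled for the time endpoints, what counts as receipt of treatment, and the time windows of the composites. A component that vanishes from a table that otherwise adds detail cannot safely be read as abbreviation, and Table 4 repeats the omission.

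**Step 3. Size.** The protocol gives no rate for this endpoint, so there is no figure to reproduce. The following is an illustration.

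Inputs, all from Sample size considerations: 320 ESC and 160 FNAST infants planned; 39.1% (ESC) and 78.8% (FNAST) pharmacologically treated in INFORM NOW. Assumption: half of the infants fall under each approach, with equal treatment rates. The article's rationale section says it is unclear whether the number treated will differ, so this is only a guide.

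- ESC: 320/2 × 0.391 = 62.6
- FNAST: 160/2 × 0.788 = 63.0
- Treated per approach: 62.6 + 63.0 ≈ 126

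Each omitted stop lowers the percentage by 1/126 ≈ 0.8 points. If #8 is reported separately for ESC and FNAST, as the Analysis plan section intends for all objectives, the denominator is about 63 and each stop is worth 1/63 ≈ 1.6 points.

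**Step 4. What could a two-approach comparison show?** With 0 events in 126 infants, the one-sided 95% upper limit is 1 − 0.05^(1/126) = 2.3% (1 − 0.025^(1/126) = 2.9% at 97.5%). Power of a two-proportion comparison with 126 per approach, ignoring clustering, for assumed taper rates:

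| Assumed taper rate | Power, doubling | Power, tripling |
|---|---|---|
| 1% | 10% | 20% |
| 2% | 15% | 37% |
| 3% | 21% | 52% |

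A by-approach summary would therefore be descriptive only.

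**Step 5. What else in the article covers these events?** Respiratory insufficiency is captured under both approaches as an event of special interest, and cumulative adverse event data go to the DSMB. Excessive sedation is not an event of special interest. Under symptom-based dosing it has no named capture unless it meets a serious adverse event definition.

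**The case against.** The best defence is that this is a wording slip in a rare, one-arm, descriptive percentage. The Dosing parameters section calls adverse events of excess sedation very uncommon and says that sedation shows before respiratory depression. On that premise some stops for respiratory depression may be charted as sedation and counted anyway, so the loss could be small or nil. This stands as a limit on the size. It does not remove the contradiction.

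A reader might go further and infer that the tables wrongly confine over-sedation to the taper arm, or that opioid harm is never compared between approaches. The document supports neither reading.

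- The taper-only scope is in the objective, the endpoint list and the population definition. It mirrors objective #7, which covers only infants started on symptom-based dosing.
- Respiratory insufficiency is collected in all enrolled infants with severity and relationship to intervention, and safety summaries go to the DSMB every 3 to 6 months and with the interim analysis. Tables of such events by approach are commonly left to the SAP, so their absence from an article is no fault.
- Leaving respiratory insufficiency out of the inpatient composite is a design choice. The article does not rank sedation or respiratory depression as the main harm.

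The supportable statement is narrower: no endpoint listed in Tables 3 and 4 compares sedation or respiratory events by approach.

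**Conclusion.** Secondary objective #8 is defined in two incompatible ways, and the tables that set the analysis carry the narrower one. Followed as written, they omit stops recorded as due to respiratory depression from a stated safety endpoint. Each omission is worth about 0.8 percentage points, or about 1.6 if ESC and FNAST are reported apart, given INFORM NOW treatment rates and equal treatment under both approaches. The number of omissions is unknown and may be zero. The defect is in reporting consistency and is worth correcting, but it does not touch the primary comparison.

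A descriptive summary by approach is a reasonable addition, chiefly because sedation short of a serious adverse event has no named capture in symptom-based infants. It is not the correction of an error.

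**What to change.** **Required.** Reconcile Tables 3 and 4 with the Secondary hypothesis and Secondary endpoints sections by restoring respiratory depression as a reason for cessation in the #8 rows. Carry the same wording into the SAP before database lock, and check that the case report form records this reason separately. This concerns only what the endpoint counts, not when treatment should be stopped. It costs a wording change in two table rows.

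**Suggested.**

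- Show the respiratory-insufficiency event of special interest by assigned approach next to the inpatient safety composite. The data are already collected in all enrolled infants.
- Where charts allow, show opioid cessation for sedation or respiratory depression by assigned approach in ITT-PT.

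Label both as descriptive, with no claim of power. The cost is one more table, plus abstraction of the reason for cessation in symptom-based infants from records that sites already review. For infants whose doses are given singly on symptoms, the SAP would need to say what counts as cessation, because there is no scheduled course to stop unless they have moved to scheduled dosing.
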